##### Feature extraction

2.3.2.1

Features were extracted using Python SciPy library (142). SciPy.stats was used for statistical parameters (e.g., mean, SD, kurtosis, and skew). SciPy.signal and SciPy.fft were used for extracting time (e.g., period amplitude) and frequency domain features (e.g., harmonics and formants). The extracted features were labeled according to the participant’s group before feeding to the machine learning classifier.

##### Choice of machine learning classifier

2.3.2.2

Many studies have demonstrated the effectiveness of using machine learning classification algorithms to accurately differentiate individuals with and without PD based on data collected through smartphone applications.

Initially, the performance of three machine learning classifiers was compared: multilayer perceptron (MLP), SVC, and random forest (RF) using the hold-out method for dataset splitting, to find which would be best suited for the Parkinson’s disease risk survey data. We used the default settings for each classifier from scikit-learn (143) version 1.3.0. The RF algorithm was chosen because it demonstrated higher accuracy in classifying PD compared to SVC and performed comparably to MLP in our preliminary analysis using tremor and gait recordings. The superior performance of the RF algorithm compared to SVC and MLP aligns with the findings of Sarkar et al. (144).

RF is a machine learning algorithm composed of an ensemble of decision trees. In a classification task, each branch of the decision tree is trained using subsets of sampled training data labeled by the predicting classes. During the learning process, decision trees perform a series of comparisons on selected input features (node splitting) until a predicting class is assigned to the feature. The final predicted class of the RF is determined by the majority of the output classes from the decision trees.

In the validation study, an RF classifier was used to predict whether activity recordings were from a person with or without PD. The forest consisted of 100 trees, and Gini impurity was used to measure the quality of splits. The maximum number of features was determined by the square root of the total number of features before searching for the best node splitting. Ten-fold cross-validation was employed to assess the generalizability of the classifiers. In each test activity, the data was divided into 90% for training and 10% for testing sets. Classifiers trained specifically for a type of activity are referred to as specialized classifiers.

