#### Digital marker selection

2.3.1

Digital markers identified for inclusion in the Parkinson’s disease risk survey were selected following a review of published studies that have used mobile devices and machine learning tools to quantify PD (83–85, 87). These studies have shown that using a combination of tests with machine learning-based analysis it is possible to distinguish subjects with PD from controls with a high degree of sensitivity and specificity. Common testing activities for PD diagnosis using smartphone applications include gait, voice, finger tapping, memory tests and questionnaires. For objective testing of motor function, the Parkinson’s disease risk survey will use a smartphone application to collect data on spoken voice, tremor, dexterity, and mobility. All selected markers are ones that ChulaPD has considerable research experience with. The final digital marker selection includes eight variables, as described in Table 4: voice vowel, voice sentences, resting and postural tremor, alternate finger tapping, “pinch-to-size” test, and gait and balance tests. The rationale for these selections and their applicability to the digital platform are summarized below.

**Table 4 tab4:** The eight selected digital markers and the number of recordings undertaken for each test activity during validation.

Activity	Subjects with PD	Control subjects
	Number of test recordings for each activity	
Voice vowel	315	183
Voice sentences	512	331
Resting tremor	211	154
Postural tremor	211	154
Alternate finger tapping	324	205
Pinch-to-size	294	205
Gait	280	202
Balance	284	201

PD, Parkinson’s disease.

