#### Digital marker validation and data analysis

2.3.2

The eight selected markers have been developed into a digital application that has been validated as described below. Validation was undertaken in a cohort of 343 people with PD (48.6% male) and 230 control subjects (27.9% were male) without PD. Participants undertook each test activity using a mobile application and data were recorded using the built-in sensors of the mobile phone, namely the accelerometer, gyroscope, microphone, and touch screen. The validation study was approved by the Human Ethics Committee of the Faculty of Medicine, Chulalongkorn University (IRB number 0804/65). All subjects gave written informed consent before the enrolment into the study, in accordance with the declaration of Helsinki. Performance on the eight test activities were recorded by each participant using a mobile application and the built-in sensors of a smartphone, namely the accelerometer, gyroscope, microphone, and touch screen. Details of how each testing activity was performed is described in Table 5.

**Table 5 tab5:** Performance methods for each of the digital marker test activities.

Marker	Description of test
Voice vowel	Participants pronounce the sustained vowel /a/, as in “*bar*,” for 10 s without holding their breath. The test is repeated three times for each participant.
Voice sentences	Participants read sentences aloud in the Thai language, such as the example sentence “*rod tid mak loey*,” which means “*The traffic is really jammed*.” The test includes a total of 25 sentences that are commonly encountered in real-life situations.
Resting tremor	Participants are instructed to place the mobile phone on one palm with the screen facing up and lay their hand in their lap. They are then asked to specify whether the device is on the left- or right-hand side by pressing on the screen. Finally, participants are instructed to keep their hand still, along with the device, for 20 s.
Postural tremor	Participants are instructed to hold the device and press on the screen to verify which side of the hand they are holding, then stretch out their arm and maintain that posture for 20 s.
Alternate finger tapping	Participants place the device on a flat surface. They are then instructed to use their index and middle fingers of one hand to tap on two circles that appear on the screen, alternating between the two fingers as quickly as possible while maintaining correct finger alternation within 10 s.

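### Cross-validation of the single-test classifiers is described without grouping by participant, so the voice-sentence AUC of 0.83 may be optimistic for new people

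*Protocol article*

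**What the plan says.** Section 2.3.2.2 of the protocol article states that "an RF classifier was used to predict whether activity recordings were from a person with or without PD". Ten-fold cross-validation is then used to judge generalizability, and the split is described in one sentence: "In each test activity, the data was divided into 90% for training and 10% for testing sets". Whether folds were formed by recording or by participant is not said.

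Section 2.3.2 gives the cohort: "Validation was undertaken in a cohort of 343 people with PD (48.6% male) and 230 control subjects (27.9% were male) without PD". Table 4 counts recordings, not people; its column header is "Number of test recordings for each activity". The two voice rows read "Voice sentences 512 331" and "Voice vowel 315 183" (PD, then controls).

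Table 5 says of the vowel test that "The test is repeated three times for each participant", and it gives the sentence test 25 sentences in total.

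Section 2.3.2.3 describes the ensemble split differently: the subjects who completed all tests (162 with PD, 128 controls) are divided 90/10. Section 2.3.2.5 and Table 6 report mean AUCs of 0.83 ± 0.04 for voice sentences and 0.82 ± 0.04 for voice vowel.

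**The concern.** A cross-validated AUC estimates performance in new people only if nobody in a test fold has also been used for training. Recordings from one speaker resemble each other for reasons unrelated to PD. The features in section 2.3.2.1 include harmonics and formants, which can carry speaker identity. If a speaker has one recording in training and another in the test fold, the forest can score the second partly by recognising the speaker, whose label it has already seen.

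The screening programme will meet only people the model has not seen. Section 2.3.2.5 uses the AUCs, together with the ensemble result, as evidence that the markers are valid. The nine AUCs in Table 6 span only 0.88 − 0.82 = 0.06, so a bias of a few hundredths in one of them would change how the tests compare.

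**Working it through.** The AUC of 0.83 cannot be reproduced without the recordings. What can be checked is whether repeats exist, how often they would cross folds, and how much that could matter.

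**1. Are there repeats? (Table 4 against the cohort in section 2.3.2)**

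Minimum repeats = recordings − people.

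- Voice sentences, PD: 512 − 343 = 169.
- Voice sentences, controls: 331 − 230 = 101.
- Together: 270 of 843, or 32%.

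This is a floor, because it assumes that all 573 people did the test. The mean per person lies between 512/343 = 1.49 and 512/162 = 3.16 (PD), and between 331/230 = 1.44 and 331/128 = 2.59 (controls). The upper figures assume that only the completers of all tests contributed.

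- Voice vowel: 315 < 343 and 183 < 230, so the counts do not prove repeats.
- The other six tests also have fewer recordings than people in both groups. Repeats there are neither proved nor excluded.

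**2. How often would siblings cross folds?**

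If recordings were assigned to ten folds at random, the recordings of a person with m of them would not all fall in one fold with probability of about 1 − 0.1^(m−1). That is 0.90 for m = 2 and 0.99 for m = 3. If the repeats were spread as evenly as possible (an assumption: 169 people with PD and 101 controls giving two each), 338/512 = 66% of PD and 202/331 = 61% of control sentence recordings would have a sibling.

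**3. How large could the effect be?**

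Illustrative simulation: 100-tree random forest, 512 + 331 recordings, 30 features of which 5 carry signal, with the signal tuned so that recording-wise AUC is near 0.83. There were three replicates per setting. The feature numbers and the within-person correlation (ICC) are assumptions.

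| Recordings spread over | ICC | Recording-wise AUC | Person-wise AUC | Gap |
|---|---|---|---|---|
| all 573 people | 0 | 0.812 | 0.802 | 0.010 |
| all 573 people | 0.3 | 0.831 | 0.821 | 0.011 |
| all 573 people | 0.6 | 0.839 | 0.808 | 0.031 |
| all 573 people | 0.9 | 0.816 | 0.676 | 0.140 |
| 290 completers | 0 | 0.811 | 0.809 | 0.002 |
| 290 completers | 0.3 | 0.833 | 0.820 | 0.013 |
| 290 completers | 0.6 | 0.860 | 0.804 | 0.056 |

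At ICC 0 there is no person effect to leak, so gaps of about 0.01 should not be read as leakage. For completers at ICC 0.9 the simulation could not be tuned to 0.83: with almost no PD signal, recording-wise AUC was 0.955 and person-wise 0.466.

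**4. Does the fold SD reveal the unit?**

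The Hanley-McNeil standard error at AUC 0.83 is 0.044 with recording-sized folds (51 PD, 33 controls) and 0.053 with person-sized folds (34 and 23). A reported SD of 0.04 from ten folds cannot tell these apart.

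**5. What is one recording?**

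Three vowel repeats from the completers alone would give 162 × 3 = 486 PD and 128 × 3 = 384 control recordings. Table 4 has 315 and 183. Twenty-five sentences each would give 162 × 25 = 4,050 and 128 × 25 = 3,200, against 512 and 331. Table 4 therefore does not count every repeat in Table 5 as a recording, and the article does not say what it does count.

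**The case against.** The strongest reply is that recording-level splitting is an inference. Classifying recordings is compatible with folds formed by person, section 2.3.2.2 does not exclude grouping, and where the article is explicit (the ensemble) it divides subjects. This stands in part: the article does not prove that people crossed folds. But it gives the tree count, the split criterion, the feature rule and the software version, and it names subjects as the unit only for the ensemble. For the single-test classifiers the described procedure has no grouping, and a reader who follows it would split recordings.

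A reader might go further and infer that the voice AUCs are inflated. The documents do not support that. No person-level AUC can be derived from them, the ICC is unknown, and at low ICC the simulated effect is negligible. The voice AUCs are among the lowest in Table 6, which neither shows nor excludes inflation. The fold SD is no evidence either, as step 4 shows.

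A reader might also extend the point to voice vowel, to all of Table 6, or to the ensemble accuracy of 0.9108. The counts prove repeats only for voice sentences. The vowel counts are compatible with one entry per person. The ensemble split is worded by subject, and its best combination in Table 7 does not use voice sentences.

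**Conclusion.** The concern holds for one result and as a risk, not as a demonstrated bias. Two facts are firm: at least 270 of the 843 voice-sentence recordings are repeats from people already counted, and the cross-validation of the single-test classifiers is described at recording level with no participant grouping. Carried out as written, it allows the same person in training and test folds, so the 0.83 may be optimistic as a measure of generalizability to new people.

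The size cannot be stated. With recordings spread over all 573 people, the simulated gap was about 0.01 at ICC up to 0.3, 0.03 at ICC 0.6 and 0.14 at ICC 0.9. It was larger at ICC 0.6 and above when fewer people supplied the recordings. These figures rest on assumed features and an assumed ICC.

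Separately, and without any assumption about folds, the recording counts in Table 4 and the repeats in Table 5 do not agree and must be reconciled before the effective sample size behind either voice AUC can be known.

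**What to change.** - Use participant-grouped, stratified ten-fold cross-validation for the specialized classifiers, with all recordings of a person in one fold. Do this at least for voice sentences and for any other test with more than one recording per person, and state the splitting unit in section 2.3.2.2.
- Replace the voice-sentence AUC in Table 6, and any other affected value, with the grouped result and a confidence interval from a bootstrap that resamples participants.
- Define one recording, add the number of participants per test to Table 4, and reconcile Tables 4 and 5 for the vowel and sentence tests.

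The cost is a changed splitting step and a re-run; no new data are needed. The reported AUC may fall. If the folds were already grouped by participant, one sentence saying so settles the splitting question, and only the definition of a recording and the participant counts remain to be added.

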##### Ensemble learning

2.3.2.3

The validation study dataset, as with many smartphone-based studies, contains missing data. Many participants only completed subsets of available tests, with less than half completing all available tests. In addition, PD symptoms are heterogeneous, meaning that patients can manifest different onset and progression patterns. To address these challenges, an ensemble classifier voting approach was employed. With this approach, the classifiers differ only in the training set based on the test activity, while the algorithm remains the same (creating a homogeneous ensemble).

Previous studies have demonstrated the benefits of accounting for the intersubject heterogeneity of PD by either combining the activity data or classifiers to enhance classification accuracy. Schwab and Karlen (145) introduced an evidence aggregation model (EAM) that integrates four trained NN models specialized in detecting PD for each test activity (walking, voice, finger tapping, and memory). This approach aims to combine several model outputs and generate a single diagnostic score. The EAM achieved an AUC of 0.85, surpassing the PD classification achieved by a single activity with single classifiers. Prince et al. (97) implemented a multi-source ensemble learning approach that utilizes three test activities (walking, voice, and finger tapping) with combined classifiers, including single neuron, random forest, convolutional NN, and deep NN. The ensemble approach classification accuracy was 82%, outperforming single activity with single or combined classifiers for PD classification. Therefore, an ensemble approach will be used for the Parkinson’s disease risk survey data analysis.

The procedure for splitting the training and testing sets for PD classification using ensemble learning is illustrated in Figure 5. Of the 343 people with PD, 162 completed all tests, while among the 230 individuals without PD, 128 completed all tests. Data from subjects who completed all tests (denoted as data t) were divided into a 90% training set and a 10% test set. The training set was combined with the data from subjects who did not complete all tests (denoted as data r) to train a specialized model for each test.

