**Figure 5 fig5:**
[figure not shown]
The procedure for splitting the training and testing sets for PD classification using ensemble learning.

A randomly sampled subset of the test set was used to predict with specialized models. This process was repeated five times for each combination of activity sets. The optimal combination of activity sets was selected based on each participant’s available recorded activities. Model outputs were then subjected to majority voting for the final classification as either PD or non-PD.

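### The voting ensemble was adopted partly to cope with missing tests, but its 0.9108 accuracy is estimated only in people who completed every test (290 of 573)

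*Protocol article*

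**What the plan says.** Section 2.3.2 describes the sample: "Validation was undertaken in a cohort of 343 people with PD (48.6% male) and 230 control subjects", 573 people in all. Section 2.3.2.3 (Ensemble learning) says of completeness: "Many participants only completed subsets of available tests, with less than half completing all available tests". It adds that PD symptoms are heterogeneous, and concludes: "To address these challenges, an ensemble classifier voting approach was employed". Missing tests are thus one of two stated reasons for the method.

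The same section gives the counts, "Of the 343 people with PD, 162 completed all tests, while among the 230 individuals without PD, 128 completed all tests", and the split: "Data from subjects who completed all tests (denoted as data t) were divided into a 90% training set and a 10% test set". Everyone else has a different role: "The training set was combined with the data from subjects who did not complete all tests (denoted as data r) to train a specialized model", one per activity.

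On prediction, the text below Figure 5 states: "A randomly sampled subset of the test set was used to predict with specialized models". This is done five times for each combination of activities. It also says: "The optimal combination of activity sets was selected based on each participant", and the sentence goes on to the recordings that the participant has available. The final class is a majority vote.

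Section 2.3.2.5 and Table 7 report a best mean accuracy of 0.9108 (SD 0.012357) for questionnaire, voice vowel, rest tremor, gait and balance. That section takes the results as confirming the validity of the markers and the testing system. The closing paragraph of the Discussion calls the platform validated and highly accurate for national screening.

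**The concern.** A method chosen partly because people arrive with incomplete data should be assessed on people with incomplete data. Here the split rule excludes them from assessment. The rule for choosing activities by what each person has available is never exercised on real missingness, because everyone in the test set has every recording.

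This carries into the survey. Section 2.3.2.3 says an ensemble approach will be used for the survey data, and section 2.1 includes self-administration through a downloaded app, where partial completion is foreseeable. What is at stake is whether 0.9108 can support the validity statements in section 2.3.2.5 and at the end of the Discussion for anyone who does not finish the whole battery.

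**Working it through.** **1. The plan's own figure.** The accuracy of 0.9108 cannot be reproduced: the article gives no confusion matrix and no count of tested participants. It is taken as stated.

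**2. Who is assessed.** Inputs are 343 PD and 230 controls (section 2.3.2), and 162 PD and 128 control completers (section 2.3.2.3).

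- Completers: 162 + 128 = 290; 290/573 = 50.6%.
- Non-completers: 573 − 290 = 283; 283/573 = 49.4%.
- By group: 343 − 162 = 181 PD and 230 − 128 = 102 controls.
- The text's statement that fewer than half completed everything holds for PD (162/343 = 47.2%) but not for the whole cohort.

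All 283 are in data r, so they train the models and are never in an ensemble test set.

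**3. How many could supply the listed combinations.** Table 4 gives 211 PD and 154 control recordings for rest tremor, and the same for postural tremor. At one recording per person or more, at least 343 − 211 = 132 PD and 230 − 154 = 76 controls lack each tremor test: 208/573 = 36%. Every row of Table 7 includes rest or postural tremor. Each listed accuracy therefore belongs to a set of tests that at least 36% of the cohort could not supply in full.

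**4. Possible effect on accuracy.** Whole-cohort accuracy = (290 × 0.9108 + 283 × a)/573, where a is the accuracy in non-completers. The article does not give a, so these values are assumptions that show the range:

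| Assumed a | Whole-cohort accuracy |
|---|---|
| 0.95 | 0.930 |
| 0.9108 | 0.911 |
| 0.85 | 0.881 |
| 0.80 | 0.856 |
| 0.70 | 0.807 |

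**5. Precision.** SE = √(p(1 − p)/n) with p = 0.9108.

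- n = 290 (all ten folds of completers pooled): √(0.9108 × 0.0892/290) = 0.0167; 95% half-width about 3.3 points.
- n = 573: √(0.9108 × 0.0892/573) = 0.0119; half-width about 2.3 points.
- Ratio: √(573/290) = 1.41.
- If only one 10% split is tested (about 29 people), SE = 0.053.

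The text describes a 10% test set and a random subset of it, while Table 7 is labelled 10-fold cross-validation, so the number tested is not clear. The SD of 0.012357 is the spread over five re-drawn test sets. It is not a sampling error for new participants.

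**The case against.** The best defence is that comparing activity combinations on the same people requires people who have every activity. Table 7 is such a comparison, and its five-, seven- and eight-activity sets all lie between 0.90 and 0.91, so the leading combinations lose little when activities are left out. This stands as a reason to rank combinations on completers. It does not make the resulting figure an accuracy for a method meant for incomplete data: setting aside a recording from someone who supplied it is not the same as assessing someone who did not.

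It can also be said that Figure 5 is not shown and that reporting by completeness may be left to a fuller plan. But the split is stated in the text as a rule, and results are reported from it, so the point does not rest on an omission.

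Several stronger readings are tempting, and the documents do not support them:

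- *That 0.9108 is biased.* No ensemble accuracy in non-completers is given, so a bias can be neither shown nor signed.
- *That people missed tests because they could not do them.* The article gives no such reason. In Table 4 the paired tremor tests have equal and lowest counts while gait has many more recordings (280 PD, 202 controls), which fits logistical causes at least as well.
- *That completion depends on disease status.* It was 47.2% in PD and 55.7% in controls, with p = 0.048 uncorrected, 0.059 with continuity correction and 0.050 by Fisher's test. This is borderline, and a difference in case mix does not by itself bias TPR or TNR.
- *That 283 people were never tested at all.* This holds for the ensemble only. The single-activity classifiers in Table 6 were cross-validated with no stated restriction to completers.

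**Conclusion.** The point holds in this limited form. The ensemble was adopted partly because of missing tests, yet its accuracy was estimated only in the 290 of 573 people with none missing. The other 283 (181 PD, 102 controls) contribute to ensemble training alone. The 0.9108 is a completers' accuracy; its value for people with missing tests is unknown, and so are the size and direction of any bias for the screened population. The loss of precision, a factor of 1.41 in the standard error, is secondary. It assumes that all folds are pooled and that accuracy stays near 0.91 once non-completers are included. The evaluation should be extended, and the validity claims should go no further than it supports.

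**What to change.** Assign all 573 participants to cross-validation folds, with all of a person's recordings in the same fold. Train the activity-specific models on the remaining folds. Classify each held-out person by voting over the tests that person actually has, under the rule to be deployed. Report TPR, TNR and accuracy with confidence intervals overall, and separately for completers and non-completers.

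Keep the completers-only analysis for ranking activity combinations and as a sensitivity analysis. Limit the validity statements in section 2.3.2.5 and the final paragraph of the Discussion to what the extended evaluation shows.

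The cost is a re-run on labelled data already held. Training data per fold falls slightly: from about 261 + 283 = 544 people (90% of 290, plus all non-completers) to about 516 (90% of 573) with ten folds. The headline accuracy may turn out lower.
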